## Abstract

**Background::**

Rotator cuff injury is the most common cause of shoulder dysfunction. Despite the continuous advancement of surgical techniques, the incidence of re-tearing after rotator cuff repair is still high. The main reason is that it is difficult to reconstruct the normal tendon bone interface and the process is slow, and the application of tissue engineering technology can promote tendon and bone healing. This study will evaluate the effect of the bionic double membrane stent on the rotator cuff healing after arthroscopic rotator cuff repair.

**Methods::**

This is a prospective randomized controlled trial to study the effect of biomimetic double-layer biofilm stent on rotator cuff healing. Approved by the clinical research ethics committee of our hospital. The patients were randomly divided into 1 of 2 treatment options: (A) a biomimetic double-layer biofilm stent group and (B) a non-bionic dual-layer biofilm stent group. Observation indicators include: visual analog scale score, University of California Los Angeles score, American Shoulder & Elbow Surgeons score and Constant-Murley score. Data were analyzed using the statistical software package SPSS version 16.0 (Chicago, IL).

**Discussion::**

This study will evaluate and evaluate the effect of the bionic double-layer membrane stent on the rotator cuff healing after arthroscopic rotator cuff repair. The results of this experiment will provide new treatment ideas for promoting rotator cuff tendon bone healing.

**OSF Registration number::**

DOI 10.17605/OSF.IO/FWKD6

## Introduction

1

Rotator cuff tear refers to the continuous interruption of cuff like structure formed by the tendons of supraspinatus, infraspinatus, subscapularis and teres minor, due to trauma, degeneration and strain, impact, blood supply damage and other reasons, which causes shoulder pain and limited movement as the main clinical manifestations. It mostly occurs in middle-aged and elderly people, with an incidence rate of 6% in the younger than 60-year-old age group, and 30% in the older than 60-year-old age group,^[1]^ In asymptomatic people, the incidence also increases with age.^[2]^ The treatment of rotator cuff injury is complicated, and 1-stage repair is feasible for patients who have failed non-surgical treatment.^[3]^ Arthroscopic rotator cuff repair has become the “gold standard” for rotator cuff injury repair, and has the advantages of less trauma and fewer complications.^[4]^

With the deepening of the understanding of the disease and the development of surgical techniques, the rotator cuff repair has achieved satisfactory clinical results, but the postoperative imaging follow-up found that the success rate of biological repair of anatomical structures is low.^[5]^ There are many reasons for the failure. The main reason is that it is difficult to reconstruct the normal tendon-bone interface and the process is slow. Compared with the normal fibrocartilage bone-tendon junction, the scar connection formed after traditional surgery has significantly lower strength,^[6]^ Although this kind of scar can reshape the fibrocartilage structure, the process often takes as long as 6 months to 1 year.^[7]^ In order to make postoperative tendon healing more firm and rapid, it is necessary to find and apply new methods to provide an ideal condition to improve the activity of tissue cells around the rotator cuff healing site and rebuild the biomechanical function of the tissue.

At present, biological methods and materials based on growth factors, repair scaffolds, and stem cells have become the research hotspots of strategies to promote rotator cuff tendon bone healing.^[8–10]^ The biomimetic double-layer biofilm scaffold is a biomimetic periosteum that combines growth factors and bioactive stem cells. It controls the release of bone morphogenetic protein 2 (BMP-2) and vascular endothelial growth factor (VEGF) and platelet derived growth factor (PDGF) form specific expression, combined with the differentiation of bone marrow mesenchymal stem cells to help the regeneration of cartilage at the tendon-bone interface and promote tendon-bone healing.

In this study, a randomized controlled trial will be used to observe the effect of the biomimetic double-layer biofilm stent on the healing of the rotator cuff after arthroscopic rotator cuff repair, and to evaluate its long-term efficacy through follow-up and explore its effectiveness in promoting tendon bone healing after rotator cuff repair.

## Materials and methods

2

### Study design

2.1

This is a prospective single-center randomized controlled trial to study the effect of a biomimetic double-layer biofilm stent on the healing of the rotator cuff after arthroscopic rotator cuff repair. The research protocol will follow the Declaration of Helsinki and comprehensive trial reporting standards.^[11]^ The flow chart is shown in Figure 1. And the study has been approved by the clinical research ethics committee of our hospital.

**Figure 1 F1:**
[figure not shown]
Flow diagram.

### Ethics and registration

2.2

This research program is in accordance with the Helsinki Declaration and approved by the Clinical Research Ethics Committee of our hospital. This protocol has been registered in open Science Framework (OSF) (Registration number: DOI 10.17605/OSF.IO/FWKD6). All patients need to sign a written informed consent before they are randomly assigned to continue the trial.

### Sample size

2.3

The calculation of the sample size is based on the visual analog scale (VAS)score results 1 month after the operation. According to the pre-test results, the average score of the experimental group is estimated to be 3.4 points and the standard deviation is 1.8. The control group averaged 4.6 and the standard deviation is 1.9. This study is a non-inverse design, 1-sided test, α =0.025, power = 90%, through calculation, each group needs 50 patients in total, and the estimated withdrawal rate is 20%. Each group will include 63 patients.

### Patients

2.4

Inclusion criteria: ①Age 45 to 70 years; ②Shoulder joint pain, active flexion and lifting weakness, affecting work and daily life, non-surgical treatment for more than 6 months, and non-surgical treatment for more than 6 months; MRI examination confirmed full-thickness rotator cuff tear ③Patients undergoing arthroscopic rotator cuff repair for the first time.

Exclusion criteria: ①Partial tear; ②Huge or irreparable tear; ③With nerve injury; ④Biceps long head tendon injury; ⑤Shoulder joint osteoarthritis, rheumatoid arthritis, etc.; ⑦ Those who have a history of shoulder surgery and a history of mental illness.

All patients participating in the study will be informed of the method, purpose and possible risks of the study. At the same time, they need to sign a written informed consent. They are free to choose whether to continue the trial at any time.

### Study design

2.5

Eligible participants were randomly assigned to the treatment group or the control group at a ratio of 1:1 using a random tool based on the central network. Randomization was performed without any stratification generated by independent statisticians who are not involved in trial implementation or statistical analysis using SAS 9.3 software (SAS Institute, Cary, NC). The clinical research coordinator enters the participant information on the tablet and Was given a random number. The research assistant gets the participant's assignment from the computer. Throughout the research process, the research assistant is responsible for screening, recruiting participants, and assigning random numbers to the participants who have been included. The result assessor is responsible for the assessment of the scale. Except for the surgeon, all doctors, anesthesiologists, research assistants, participants, intervention supervisors, and statisticians who conduct statistical analysis, the division of personnel is unknown.

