#### Data collection and management

2.8.1

During each follow-up, 1 to 2 assistants will collect the follow-up data according to the evaluation criteria, and record them clearly in a pre-designed form combined with the basic information of patients. The information and data of all patients will be collected and stored in a fixed storage room to protect the confidentiality before, during and after the trial. Access to the database is limited to the researchers of this research group.

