## Discussion

3

At present, the incidence of rotator cuff nonhealing and re-tearing after rotator cuff injury is still high.^[17]^ Most scholars believe that poor healing of the tendon at the stop of the rotator cuff is a key factor affecting the effect of surgery. In recent years, with the rapid development of tissue engineering, the repair of the tendon-bone interface of rotator cuff injuries has also made great progress. Different treatment methods have their own advantages, and the combined application of multiple strategies may be the most effective method.^[18]^

The biomimetic double-layer biofilm scaffold is prepared using natural small intestinal submucosa and chitosan, and Poly (lactic co glycolic acid) (PLGA) microspheres are used as controlled-release carriers of BMP-2, VEGF and PDGF. PLGA microspheres which could simulate the controlled release of BMP-2 in vivo and PLGA microspheres with sequential controlled release of VEGF and PDGF were combined into the inner and outer layers of the double-layer membrane scaffold respectively, and the bone marrow mesenchymal stem cells are inoculated in the periosteum The scaffold is used to construct a biomimetic periosteum with biological activity and loaded with stem cells, and then transplant it to the tendon-bone interface to promote tendon-bone healing. The biomimetic double-layer biofilm scaffold combines growth factors, repair scaffolds, and stem cells to reflect the combined application strategy. Therefore, this study will provide new ideas for the treatment of poor tendon bone healing after rotator cuff injury, and it is expected to reduce the incidence of rotator cuff nonunion and re-tear.

This study also has the following limitations: due to the influence of intervention methods, this study cannot be strictly double-blind, which may affect the results; lack of quantitative evaluation indicators for rotator cuff healing and secondary arthroscopic observation; the current protocol has a short follow-up time. If necessary, we will plan to extend the follow-up to observe the medium and long-term effects.

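### The research assistant is listed as unaware of allocation yet retrieves it, and the plan does not secure blinded collection of the outcome scores

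*Protocol article*

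**What the plan says.** Section 2.5 (Study design) describes the handling of allocation and the blinding in one paragraph.

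- On access to the allocation: "The research assistant gets the participant's assignment from the computer".
- On the same role's other tasks: "the research assistant is responsible for screening, recruiting participants, and assigning random numbers to the participants who have been included".
- On scoring: "The result assessor is responsible for the assessment of the scale".
- On blinding: "Except for the surgeon, all doctors, anesthesiologists, research assistants, participants, intervention supervisors, and statisticians who conduct statistical analysis, the division of personnel is unknown".

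Section 2.8.1 (Data collection and management) then says: "During each follow-up, 1 to 2 assistants will collect the follow-up data according to the evaluation criteria". It does not say whether these are the research assistants, the result assessor or other staff.

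The Discussion lists as a limitation: "due to the influence of intervention methods, this study cannot be strictly double-blind, which may affect the results".

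**The concern.** A person who retrieves each assignment cannot also be unaware of it, so the blinding rule cannot be carried out as written for at least one role. That role also has the widest contact with patients before surgery, through screening and recruitment.

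The outcomes make this matter. Under section 2.7 the patient marks the pain scale, and the three shoulder scores combine pain with function and, in two of them, strength and motion. All four are self-reported or drawn out by an examiner. The control group has conventional repair only, and the trial is admitted not to be strictly double-blind. Keeping allocation away from whoever collects and scores the outcomes is then the main protection left, and the text does not establish it. If knowledge of the arm did reach the scoring, the likely direction would be towards the new scaffold, and no analysis could remove it afterwards.

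**Working it through.** **The roles side by side**

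| Role | Task | In the blinding sentence? |
|---|---|---|
| Surgeon | Operates | Named as the exception |
| Research assistant | Screens, recruits, assigns random numbers, obtains the assignment (2.5) | Yes |
| Result assessor | Scores the scales (2.5) | No |
| Follow-up assistants, 1 to 2 | Collect and record follow-up data (2.8.1) | Only if they are the research assistants; not stated |
| Anesthesiologists, intervention supervisors | Presence at implantation not described | Yes |
| Participants, analysing statisticians | – | Yes |

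**Two readings of the blinding sentence**

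1. Natural reading: only the surgeon is the exception, and everyone else listed is unaware. The research assistant is then declared unaware while receiving each assignment, which is a contradiction.
2. Literal alternative: the whole list is the exception. The contradiction disappears, but participants and the analysing statisticians then know the allocation too, and the pain scale on which the sample size rests would be marked by patients who know their arm.

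Neither reading gives a sound blinding rule.

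**Outcome collection.** The result assessor's blinding is stated nowhere under the natural reading. The only assistant whose duties are described elsewhere is the research assistant, and nothing separates that role from the assistants of section 2.8.1.

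**The plan's own figure, checked first.** Inputs from section 2.3: means 3.4 and 4.6 (difference 1.2), standard deviations 1.8 and 1.9, one-sided α 0.025, power 90%, withdrawal 20%.

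- n per group = (1.960 + 1.282)² × (1.8² + 1.9²) / 1.2² = 10.51 × 6.85 / 1.44 ≈ 50
- 50 / (1 − 0.20) = 62.5, rounded up to 63

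Both match the plan. These inputs can therefore carry the illustration below, but they say nothing about blinding.

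**Illustration only.** Suppose there is no true effect and assessment shifts the group difference by b points.

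- Standard error = √((1.8² + 1.9²) / 50) = √0.137 = 0.370
- Two-sided false-positive rate = P(|Z + b/0.370| > 1.96)

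| Assumed b (0-10 scale) | b / 0.370 | False-positive rate |
|---|---|---|
| 0 | 0 | 5.0% |
| 0.2 | 0.54 | 8.4% |
| 0.3 | 0.81 | 12.8% |
| 0.5 | 1.35 | 27.2% |

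The values of b have no source in the document. The 0-10 scale is also an assumption: it fits the means in section 2.3, whereas section 2.7 describes marking from 0 to 100.

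**The case against.** Much can be said for the plan.

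- **A separate scorer is named.** Section 2.5 gives the scales to a result assessor, and the assistants in section 2.8.1 are said to collect and record data, which is compatible with someone else scoring. This stands. A reader might infer that the person who holds the allocation will score the outcomes; the document does not say so. It only fails to rule it out.
- **No assessor blinding is promised.** A reader might infer that the plan claims a blinded assessor and breaks that claim. It does not: the assessor is simply absent from the list. What can be said is that assessor blinding is neither stated nor secured.
- **The blinding sentence is garbled.** This also stands, and the contradiction depends on its natural reading. The other reading does not rescue the plan, because it unblinds participants and the analysing statisticians.
- **The limitation is disclosed.** The Discussion attributes it to the nature of the intervention, which fits the surgeon's knowing the arm. It is not an admission that assessment is unblinded, but it does not settle the conflict between roles either.
- **The illustration is weak evidence.** The biases are assumed, and the pain scale is marked by the patient, so it is the score least open to bias from an examiner. The two-sided 5% baseline also differs from the one-sided 0.025 test in section 2.3. All of this stands; the point does not rest on those rates.
- **The article is a condensed report.** Brevity would excuse an omission. It does not excuse two statements in one paragraph that conflict.

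**Conclusion.** The point holds in a limited form. On the natural reading of section 2.5, the research assistant both obtains the allocation and is unaware of it, which is impossible. With the result assessor missing from the list and the follow-up assistants unidentified, the text allows a person who knows the allocation to collect subjective scores. Blinded outcome assessment is not secured as written; that is weaker than saying it is absent or already breached.

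The size cannot be derived from the document. The rates of 8.4% to 27.2% show only that a small systematic shift would matter at 50 per group, given the assumed biases of 0.2 to 0.5 points and the assumed 0-10 scale. They do not estimate the error rate of this trial.

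The roles should be settled before follow-up scoring begins.

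**What to change.** Rewrite the role description in section 2.5 and align section 2.8.1 with it.

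1. Have the central system release the assignment to the operating surgeon, and to nobody who collects or scores outcomes. If the research assistant must receive it, take that role off the blinded list and bar it from follow-up data collection.
2. Say who the follow-up assistants are, and state that they and the result assessor have no access to the allocation or the operative notes.
3. Restate the blinded list in one unambiguous sentence. Add the result assessor, and leave out anyone who sees the implantation. Whether that applies to the anesthesiologists and intervention supervisors depends on whether they are present, which the document does not say.
4. Describe the trial by the roles that are actually blinded, so that section 2.5 and the Discussion agree.

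The cost is small: a clarification of wording and a change of system permissions. The surgeon, coordinator, research assistant and result assessor are already in the plan. The sample size does not change.

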### Intervention measures

2.6

(1)Arthroscopic evaluation: The glenohumeral joint will be examined through the posterior approach, and the rotator cuff joint will be examined through the anterior approach. The posterior approach is used to enter the subacromial space and the lateral approach was established. The shape of rotator cuff tear and the degree of tendon retraction are observed from the posterior and lateral approach respectively, and the rotator cuff tear is comprehensively evaluated. All patients are identified as full-thickness tears under arthroscopy without large and irreparable tears.(2)Conventional arthroscopic repair: The operation will be completed by the same surgeon. Under general anesthesia, the patient takes the lateral decubitus position, disinfects, spreads the towel, and traction of affected limb. After exploring the joint cavity through the conventional arthroscopic approach, the patient enters into the subacromial region. The patients with subacromial impingement sign are given conventional subacromial decompression, and the rotator cuff break and rotator cuff insertion bone surface are freshened under the microscope, and the rotator cuff tissue is repaired with single or double row wire anchors.(3)Implantation of the biomimetic double-layer biofilm scaffold: the bone surface of the damaged rotator cuff is freshened, and the membrane containing BMP-2 microspheres is placed on the humerus side, and the membrane containing VEGF and PDGF poly lactic-co-glycolic acid (PLGA) microspheres is placed on the tendon side.

The experimental group underwent conventional arthroscopic repair after implantation of the biomimetic double-layer biofilm stent, and the control group only underwent conventional arthroscopic repair. There were no special differences in other consumables during the operation.

### Evaluation Criteria and Efficacy Judgment

2.7

(1)VAS:^[12]^VAS is often used to measure pain intensity.^[13]^ The patient will be asked to mark a point between 0 and 100, where 100 means maximum pain (far right) and 0 means no pain (far left);(2)American Shoulder & Elbow Surgeons score.^[14]^ The American Shoulder & Elbow Surgeons score includes pain (50 points) and life function (50 points). The full score is 100 points. The higher the score, the better the shoulder joint function;(3)University of California Los Angeles score:^[15]^ Including pain, function, muscle strength and range of motion of the shoulder joint. The total score is 35 points, the higher the score, the better the shoulder joint function;(4)Constant-Murley score:^[16]^ It is the shoulder joint scoring method uniformly adopted by the European Society of Shoulder and Elbow Surgery. It consists of 4 subscales: pain (15 points), muscle strength (25 points), functional activity (20 points) and shoulder joint mobility (40 points). The total score is 100 points, the higher the score, the better the shoulder joint function.(5)X-ray evaluation of postoperative shoulder joint anatomy, MRI evaluation of tendon anchor loosening and displacement and rotator cuff healing.(6)Incision healing grade, incidence of adverse reactions (such as incision infection, anchor loosening, rotator cuff tearing, etc).

### Postoperative rehabilitation and follow-up

2.8

All patients undergo rehabilitation training according to the standard plan. Postoperatively, the shoulder joint fixation device is used to fix the affected shoulder at 30° internal rotation and 20° abduction. From 0 to 6 weeks after surgery, mainly passive activities, the main actions: pendulum, forward bend, lift and external rotation, forward flexion and abduction should not exceed 90°; active exercise will be started after 6 weeks; physical labor is allowed after 6 months or sports. After 3, 6, and 12 months outpatient follow-up, X-ray and MRI examination of the shoulder joint are performed.

#### Data collection and management

2.8.1

During each follow-up, 1 to 2 assistants will collect the follow-up data according to the evaluation criteria, and record them clearly in a pre-designed form combined with the basic information of patients. The information and data of all patients will be collected and stored in a fixed storage room to protect the confidentiality before, during and after the trial. Access to the database is limited to the researchers of this research group.

#### Statistical analysis

2.8.2

We will use SPSS 16.0 statistical software for statistical analysis. Continuous variables were described as the mean ± standard deviation, and differences between groups were analyzed using a series of 1-way analysis of variance (ANOVA) with Bonferroni post-hoc test, while differences between groups over time were analyzed using multi-way ANOVA with Bonferroni post-hoc test. Categorical variables were described as the number (%), and were analyzed by Fisher exact test. A *P* value of < .05 was considered statistically significant.

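### With two arms the Bonferroni step after the one-way ANOVAs adjusts nothing, no outcome is named primary, and four scales are each judged at P < .05

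*Protocol article*

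**What the plan says.** The design has two arms. The Abstract states that "The patients were randomly divided into 1 of 2 treatment options", and section 2.5 has participants "randomly assigned to the treatment group or the control group at a ratio of 1:1".

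For continuous outcomes, section 2.8.2 gives two analyses in one sentence. The first is that "differences between groups were analyzed using a series of 1-way analysis of variance (ANOVA) with Bonferroni post-hoc test". The second is that "differences between groups over time were analyzed using multi-way ANOVA with Bonferroni post-hoc test". One threshold serves all tests: a P "value of < .05 was considered statistically significant".

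The Abstract lists the outcomes without ranking them: "Observation indicators include: visual analog scale score, University of California Los Angeles score, American Shoulder & Elbow Surgeons score and Constant-Murley score". Section 2.7 describes the same four scales, again unranked, and adds imaging, incision healing and adverse events. Neither place, nor any other in the article, calls an outcome primary. Section 2.3 sizes the trial on VAS at 1 month but gives it no other status.

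On timing, section 2.8 reads "After 3, 6, and 12 months outpatient follow-up" and attaches X-ray and MRI to those visits. Section 2.8.1 adds: "During each follow-up, 1 to 2 assistants will collect the follow-up data according to the evaluation criteria". No 1-month visit is listed.

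**The concern.** A reader who sees a Bonferroni test named twice will assume that multiplicity has been handled. For the treatment comparison it has not. A Bonferroni post-hoc test after a one-way ANOVA corrects for the number of pairs of groups, and here there is one pair. The multiplicity that matters for an efficacy claim lies across the four scales, and the stated correction does not reach it.

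The lack of a named primary outcome makes this matter. With one deciding comparison, the other scales would be supportive and their error rates secondary. Without it, each of the four stands on the same footing at P < .05, and the plan does not say which result answers the trial's question. The sizing basis does not settle this: it is a pain score at a time point absent from the follow-up schedule, while the stated aim is rotator cuff healing.

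**Working it through.** **The plan's own figure.** Inputs from section 2.3: means 3.4 and 4.6 (difference 1.2), SDs 1.8 and 1.9, one-sided alpha 0.025, power 90%, withdrawal 20%.

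- Average variance: (1.8² + 1.9²)/2 = (3.24 + 3.61)/2 = 3.425, so SD = 1.851.
- n per group = 2 × 3.425 × (1.960 + 1.282)² / 1.2² = 49.98, rounded up to 50.
- With withdrawal: 50/0.8 = 62.5, rounded up to 63.

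Both stated figures are reproduced. One-sided 0.025 and two-sided 0.05 give the same n, so section 2.3 and the P < .05 threshold agree if the latter is two-sided. The sample size holds for one comparison tested once.

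**What the Bonferroni step does.** The factor is the number of pairs, k(k − 1)/2.

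- One-way ANOVA, two groups: 2 × 1/2 = 1. In a simulated two-group data set the ANOVA, t-test and Bonferroni P values were all 0.0604.
- Multi-way ANOVA, contrasts among three visits: 3 × 2/2 = 3. The correction is real here.
- Multi-way ANOVA, all pairs of the six group-by-visit cells: 6 × 5/2 = 15. Section 2.8.2 does not say that these pairs are compared.
- Group effect in the multi-way ANOVA: two levels, so again 1.

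Each model is fitted to one scale, so no version spans the four scales.

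**Size of the uncontrolled error.** If m tests at 0.05 are independent and no effect exists, the chance of at least one false positive is 1 − 0.95^m.

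- Four scales at one visit: 1 − 0.95⁴ = 0.185.
- Four scales at three visits, each tested separately: 1 − 0.95¹² = 0.460.

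The article gives no correlations, so a common correlation ρ between the test statistics was assumed and varied (equicorrelated normal statistics, 400,000 draws, two-sided 0.05):

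| Assumed ρ | 4 tests | 12 tests |
|---|---|---|
| 0 | 18.5% | 46.0% |
| 0.3 | 17.4% | 39.7% |
| 0.5 | 15.7% | 31.9% |
| 0.7 | 12.9% | 23.2% |
| 0.8 | 11.4% | 18.5% |

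**What each remedy needs.** One named primary comparison, tested once at two-sided 0.05, keeps 50 evaluable per group (63 with withdrawal) if it is the sized one. Keeping four co-equal scales with a real Bonferroni correction means 0.05/4 = 0.0125 per test. Applying the 1.2-point VAS effect as an illustration, this needs 68 per group (68/0.8 = 85 with withdrawal), and power at 50 per group falls to 77%.

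**The case against.** The strongest objection concerns scope. The sentence in section 2.8.2 has a second half, and in the multi-way ANOVA Bonferroni can have a factor above 1. A reader might infer that the plan has no error control at all; the article does not support that. Correction of contrasts between visits may exist, and how far it reaches group differences at each visit depends on a contrast set that is not specified. This stands, and it limits the point to the group effect and to the four scales.

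The count of tests is also open. A reader might take twelve tests and 46% as the plan's error rate. The text speaks of a series of ANOVAs without saying that one is run at each visit, and the multi-way model can take time into a single analysis per scale. That the scales are recorded at every visit is a fair reading of section 2.8.1, but it is not a test plan. Independence is implausible too: section 2.7 shows that pain is part of the ASES, UCLA and Constant-Murley scores as well as being the whole of the VAS, and repeated measurements on the same patients are correlated. This stands, and it is why a range is given with the four-test case first.

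Third, a fixed sequence or Holm procedure is detail that an article may leave to a full protocol or SAP, neither of which is shown, and the sizing endpoint is often read as an implicit primary. This stands in part. The missing procedure alone would be no finding. But the article does state an adjustment that cannot adjust the two-group comparison, and the implicit primary has no visit in the schedule.

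Finally, the redundant step is harmless in itself, since it leaves the P value unchanged. That is true; the harm lies in the protection it appears to give.

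**Conclusion.** The point holds in limited form. That the Bonferroni factor is 1 in the one-way two-group comparison follows from the design and needs no assumption. That no outcome is named primary, and that no adjustment across the four scales is stated, can be read directly from the article.

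The size rests on assumption. With common correlations from 0.8 down to 0, the chance of at least one false positive is about 11% to 18.5% for four scales at one visit. If each scale is also tested separately at the three scheduled visits, which the text allows but does not state, it is about 19% to 46%. Even the lowest value is about twice the nominal 5%.

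A reader might further infer that any single significant result would be claimed as proof of efficacy. The article states no such success rule. The problem is that it states none, so a positive finding on one scale could not be weighed against a plan fixed beforehand. The sample size arithmetic is correct and is not in question.

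**What to change.** 1. Name one primary outcome at one visit, tested once at two-sided 0.05. The natural choice is the VAS comparison of section 2.3.
2. Reconcile its time point first. Section 2.3 uses 1 month; section 2.8 lists 3, 6 and 12 months. Either record VAS at 1 month, or restate the sizing basis for a scheduled visit.
3. Drop the Bonferroni post-hoc test from the one-way two-group comparison only. Where it is kept in the multi-way ANOVA, state which contrasts it covers.
4. Apply Holm or a fixed sequence to the other three scales at one visit.
5. Report the remaining comparisons descriptively with 95% confidence intervals.

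The cost is mainly wording. The secondary scales can no longer each be claimed at P < .05, and a 1-month VAS record may have to be added. If the sized comparison is kept as primary, 50 evaluable and 63 randomised per group still apply; if the sizing is moved to another visit, the assumed means and SDs must be justified for that visit and the calculation repeated.

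### The named between-group test, a one-way ANOVA, makes no use of a pre-operative score; it is valid, but ANCOVA would be more precise at little cost

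*Protocol article*

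**What the plan says.** Protocol article, section 2.8.2 (Statistical analysis), names two analyses for continuous variables. For group comparisons, "differences between groups were analyzed using a series of 1-way analysis of variance (ANOVA) with Bonferroni post-hoc test". For the course over time, "differences between groups over time were analyzed using multi-way ANOVA with Bonferroni post-hoc test". It mentions no covariate, no ANCOVA and no change from baseline, and it does not list the time points that enter either analysis.

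Section 2.5 (Study design) has patients "randomly assigned to the treatment group or the control group at a ratio of 1:1" and adds: "Randomization was performed without any stratification".

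Section 2.3 (Sample size) works from a post-operative level: "The calculation of the sample size is based on the visual analog scale (VAS)score results 1 month after the operation". Its inputs contain no baseline term.

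Section 2.8.1 (Data collection and management) describes scoring at the follow-up visits, where assistants "record them clearly in a pre-designed form combined with the basic information of patients". The article does not say whether the four scales are also scored before surgery.

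**The concern.** A one-way ANOVA with two groups is the two-sample t-test. It cannot take a covariate, so carrying out section 2.8.2 as written gives an unadjusted difference. This is a choice of method that the protocol states, not a detail left to an unseen analysis plan.

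If a patient's score before surgery predicts the score afterwards, the part of the outcome variance that it explains stays in the error term, and the confidence interval is wider than it needs to be. Unstratified randomisation does not reduce that variance by design. The over-time analysis could make use of a pre-operative value, but the text leaves open whether that value is an outcome time point, a covariate or absent. What is at stake is precision, not the validity of the test.

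**Working it through.** **Inputs (section 2.3).** Experimental arm: "the average score of the experimental group is estimated to be 3.4 points and the standard deviation is 1.8". Control arm: "The control group averaged 4.6 and the standard deviation is 1.9". One-sided α 0.025, power 90%, 50 per group, 20% withdrawal, 63 per group.

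**Step 1: reproduce the planned size.**
- Difference: 4.6 − 3.4 = 1.2.
- Pooled variance: (1.8² + 1.9²)/2 = (3.24 + 3.61)/2 = 3.425, so the SD is 1.851.
- n per arm = 2 × 3.425 × (1.960 + 1.282)²/1.2² = 49.98, which rounds up to 50.
- With withdrawal: 50/0.8 = 62.5, which rounds up to 63.

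Both stated figures are reproduced by an unadjusted comparison of two means. The planned size and the named test therefore agree, and the size does not depend on baseline adjustment.

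**Step 2: power of the named test.** Standard error with 50 completers per arm: √(3.425 × 2/50) = 0.370. Noncentrality: 1.2/0.370 = 3.24. By the noncentral t distribution with 98 degrees of freedom and two-sided α 0.05, power is 89.4%. The normal approximation gives 90.0%. The 95% CI half-width is 1.984 × 0.370 = 0.73 points.

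**Step 3: power with ANCOVA.** If ρ is the correlation between the pre-operative and follow-up score, the residual variance is 3.425 × (1 − ρ²) and the standard error is 0.370 × √(1 − ρ²), with 97 degrees of freedom. The documents give no ρ, so a range is assumed.

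| Assumed ρ | Standard error | Power | 95% CI half-width |
|---|---|---|---|
| unadjusted | 0.370 | 89.4% | 0.73 |
| 0.1 | 0.368 | 89.7% | 0.73 |
| 0.2 | 0.363 | 90.6% | 0.72 |
| 0.3 | 0.353 | 92.0% | 0.70 |
| 0.4 | 0.339 | 93.8% | 0.67 |
| 0.5 | 0.320 | 96.0% | 0.64 |

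**Step 4: check by simulation.** In 10,000 simulated trials at each of ρ = 0.3, 0.5 and 0.7, with 50 per arm and two-sided α 0.05:
- Unadjusted test: type I error 0.047 to 0.050, power 0.894 to 0.896.
- ANCOVA: type I error 0.047 to 0.051, power 0.920 at ρ = 0.3 and 0.958 at ρ = 0.5.

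Both tests hold their level. They differ only in efficiency.

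**The case against.** The strongest reply is that nothing is wrong with the named test. It is unbiased under randomisation, keeps its type I error and has close to the planned power with 50 completers. All of that stands, so this is an improvement to a valid method.

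A second reply is that the gain rests on a correlation the documents do not give. That also stands. At 0.1 to 0.2 power rises by only 0.3 to 1.2 percentage points, and a case for change that started at 0.3 would leave this out.

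Three stronger readings are tempting, and the documents do not support them:

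- *The plan throws away a baseline score it has.* The article never says that the scales are scored before surgery. A condensed article may omit this, so neither the measurement nor its absence can be shown.
- *Nothing else in the plan could use baseline.* The same sentence of section 2.8.2 names a multi-way ANOVA over time. If the pre-operative value is one of its time points, the group-by-time term would use it. The text does not settle this.
- *Chance imbalance is a further harm on top of lost precision.* At ρ = 0.5 and 50 per arm, a 1.96-SE imbalance would move the unadjusted difference by 1.96 × 0.5 × 1.851 × √(2/50) = 0.36 points. That shift is part of the sampling error already inside the unadjusted interval, so counting it separately counts one cost twice. Unstratified 1:1 allocation is not itself a defect.

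One thing survives these replies. The protocol does fix the between-group test, and that test cannot use a baseline score even if one is recorded.

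**Conclusion.** The point holds as one of efficiency. Section 2.8.2 commits the group comparisons to a one-way ANOVA without a baseline covariate and leaves the role of any pre-operative value in the over-time analysis undefined. Against 89.4% power and a CI half-width of 0.73, ANCOVA would give 92.0% and 0.70 at a correlation of 0.3, and 96.0% and 0.64 at 0.5. Below 0.3 the benefit is small.

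These figures assume the section 2.3 means and SDs, 50 completers per arm, equal allocation, a linear relation between pre-operative and follow-up score, and the assumed range of correlations. They do not show bias, an inflated error rate or too small a sample. The change is still worth making before recruitment starts: it costs very little, a pre-operative score cannot be recovered after surgery, and naming the covariate in advance removes any later choice between adjusted and unadjusted results.

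**What to change.** In section 2.8.2:

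- Replace the one-way ANOVA for each of the four scales with ANCOVA: follow-up score on treatment group, with the pre-operative score of the same scale as covariate.
- In the over-time analysis, enter the pre-operative score as a covariate and not as an outcome time point.
- Report the adjusted mean difference with its 95% CI.

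In section 2.8.1, state that VAS, ASES, UCLA and Constant-Murley are recorded before randomisation, if this is not already done. The existing data form can hold them.

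The cost is a sentence or two of text, one degree of freedom (97 in place of 98 with 50 completers per arm) and, where the scores are not already collected, one short pre-operative scoring per patient. The sample size need not change.
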